## Abstract

(1) Background: Adolescent refugees in Lebanon and Lebanese youth are both at high risk of suffering from reduced psychological well-being. Sport is an evidence-based strategy for improving mental and physical health, and climbing is a type of sport that may positively impact both. The aim of this study is to test the effect of a manualized, psychosocial group climbing intervention on the well-being, distress, self-efficacy, and social cohesion of adolescents in Lebanon. In addition, the mechanisms behind psychological changes will be investigated. (2) Methods: In this mixed-methods waitlist-controlled study, we are allocating a minimum of 160 participants to an intervention (IG) or a control group (CG). The primary outcome is overall mental well-being (WEMWBS) after the 8-week intervention. Secondary outcomes include distress symptoms (K-6 Distress Scale), self-efficacy (General Self-Efficacy Scale; GSE), and social cohesion. Potential mechanisms of change and implementation factors are being investigated through qualitative interviews with a subgroup of 40 IG participants. (3) Conclusions: The results may contribute to knowledge of sports interventions and their effects on psychological well-being and will provide insights regarding low-intensity interventions for supporting adolescent refugees and host populations in conflict-affected settings. The study was prospectively registered at the ISRCTN platform (current-controlled trials). ISRCTN13005983.

## 1. Introduction

Lebanon is severely burdened by an ongoing economic crisis, political gridlock, hyperinflation, unemployment, and an outdated infrastructure. Problems have been significantly amplified by the 2020 port explosion and the COVID-19 pandemic. In an attempt to protect an already underfinanced healthcare system, the Lebanese government enforced a strict lockdown that may have saved lives from COVID-19, but led to an exacerbated crisis in addition to the already struggling economy, and interrupted education for approximately 1.5 million children [1]. The Russian invasion of Ukraine in 2022 exacerbated the situation through a wheat crisis and an acute shortage of bread. People were forced to stand in line for several hours to obtain sufficient staples to feed a family [2]. At the same time, Lebanon has taken in the more refugees in relation to its population size than other country in the world [2]. Among these refugees are an estimated 1.5 million displaced Syrians and another 0.5 million Palestinians. More than 50% of the refugee population in Lebanon are children [3].

In the Bekaa region of Lebanon, where most Syrian refugees reside, the situation for both the Lebanese host community and Syrian refugees has deteriorated throughout the ongoing economic crisis. Nearly 70% of income-generating household members in the Bekaa are children between the ages of 4 and 18 years, and therefore, around 40% of Syrian refugee children are not enrolled in any type of schooling [1]. Concurrently, 77% of Lebanese and 99% of Syrian households in Lebanon reported not having sufficient food or money in March 2021 [4]. Due to the worsening economic and political situation, there is a deterioration of the relationship between the Lebanese host and the Syrian refugee communities [5].

Adverse living conditions, human rights violations, and ongoing stressors have a detrimental effect on mental health. Children and adolescents are an especially vulnerable group [6]. Considering that mental and physical symptoms are interrelated [7], and that poor mental health is associated with a reduction in life expectancy [8], protecting and promoting the mental health of adolescents, especially in resource-poor settings is of high importance. Services offered by nonprofit organizations and national health service providers typically have a limited reach, leaving many young refugees without access to support programs [9]. There is a need for scalable, low-threshold, evidence-based psychosocial interventions that simultaneously strengthen mental health in addition to physical health [10].

In nonhumanitarian settings, the positive effects of sport and physical activity have been widely researched. Regular participation in physical activity and sport is associated with improvements in symptoms of depression in adults [11] and adolescents [12], post-traumatic stress symptoms [13], anxiety disorders [14], eating disorders [15,16], and substance dependence [17]. In addition, physical activity can protect against the onset of mental illness [18,19]. Especially for disadvantaged youth, sport is a protective factor [20]. Physical activity is further capable of improving self-esteem, energy levels, well-being, and overall quality of life [21,22,23]. As a psychosocial intervention, sports programs create a healthy environment where participants can manage their stress in a positive way, form team friendships, and experience a sense of belonging. Moreover, regular physical activity can improve self-efficacy, emotional intelligence [24,25], and it is positively correlated with social cohesion [26]. Regular physical activity is associated with psychological well-being and reduced levels of psychological distress [27,28]. The existing literature illustrates that sport and physical activity in the context of humanitarian assistance are capable of improving the psychosocial well-being of young refugees [29]. For example, a Capoeira dance/martial arts program for young refugees in Australia had positive effects on interpersonal skills, sense of responsibility, and discipline [30]. Furthermore, a surf therapy program showed improvement in children’s well-being [31]. Specific cultural beliefs about physical activity, which often arise from different ethnic identities and exposures, play a strong role in people’s decision to adopt a physical activity program [32,33,34,35]. For survivors of torture, trauma-sensitive soccer proved to be a critical factor for regaining access to one’s body, building social relationships, and learning to cope with stressful events [36]. Moreover, a study involving children and adolescents found that after disasters, sports and exercise are able to promote emotional and social stabilization and improve resilience [37]. However, all these previous studies relied on uncontrolled pre-post methodologies. Sport is also a highly accepted and culturally appropriate way to reduce stress, yet access to sport is often severely limited, particularly in camp environments [9,23], which is a risk factor for poor mental health in and of itself [38]. It has also been shown that opportunities to participate in sports are usually limited to specific refugee groups such as able-bodied young men, which limits participation of other groups in particular, children, and females [39]. Therefore, targeted programs are required. Unfortunately, existing research largely focuses on refugees living in high-income countries, despite low- and middle-income countries (LMICs), such as Lebanon, hosting the greatest number of refugee and the associated need for health promotion initiatives [28].

Climbing as therapy has been shown to reduce symptoms of depression in adults in at least two studies involving randomized controlled trials [40,41] and has shown a tendency to improve mental health in general in a recent meta-analysis [42]. It also has the potential to enhance feelings of self-efficacy [43], which is often limited in disadvantaged youth. This paper presents the design of a mixed-methods, waitlist-controlled intervention study on psychological well-being, distress, and self-efficacy, as well as social cohesion in underprivileged adolescents (refugees and the host community) living in Lebanon.

## 2. Methods

### 2.1. Overall Aims

The aim of the study is to test the effectiveness of a climbing intervention among adolescent locals and refugees living in the Bekaa region of Lebanon. We hypothesized that the climbing intervention will have a beneficial effect on participants’ psychological well-being. Additionally, we are investigating the impact of the intervention on, and the relationships between, self-efficacy, psychological distress, participants’ perceptions of other nationalities (Syrian, Lebanese, Palestinian), and social cohesion.

To gain insight into the modes of action and potential benefits that are specific to culture and living conditions as well as barriers and facilitators of the intervention, we are conducting qualitative interviews with a subsample of participants, balanced for age, sex, and intervention subgroup.

### 2.2. Trial Outcomes and Hypothesis

#### 2.2.1. Primary Outcome

Psychological well-being is being measured with the WEMWBS [44]. The participants in the intervention group (IG) are expected to benefit significantly more in terms of their psychological well-being than adolescents assigned to the control group (CG; effect size of Cohen’s d ≥ 0.55).

#### 2.2.2. Secondary Outcomes

Symptom severity of distress, self-efficacy, and social cohesion outcomes are being measured. Additionally, qualitative interviews are being conducted with at least 30 members of the IG and analyzed using content analysis as described by Mayring [45].

#### 2.2.3. Study Design and Setting

The research is designed as a waitlist-controlled trial, with the implementation of a manualized climbing intervention for Lebanese adolescents and adolescent refugees living in the Bekaa region of Lebanon. The plan is for the CG not to receive any study-specific intervention while the IG receives the intervention, but the CG members will be invited to participate in an upcoming cycle of the climbing program. Members of the CG will, therefore, be offered the same intervention as the IG after their waiting period. For the individual participant, the study duration will be up to approximately 12 weeks with 8 weeks of intervention (see Figure 1), followed by the voluntary participation of the CG members in the intervention. The procedure involves administering surveys to both groups (IG and CG) before the intervention begins (t0, pretest) and immediately after the intervention ends (t1, posttest). During the second half of the intervention period, qualitative semi-structured interviews will be conducted with members of the IG focusing on modes of action and outcomes of the intervention. The participant timeline is presented in Figure 1. Trial Registration Data are presented in Table 1 (ISRCTN13005983, registered April 2022, registered prospectively).

### 2.3. Eligibility Criteria

The target population of the study includes adolescents (refugees and those from the host community) living in the Bekaa valley in Lebanon.

Inclusion criteria:Between the ages of 14 and 19;Informed consent for participation in the study from adolescents as well as legal guardians (adult relatives), particularly for data collection, pseudonymized data storage, and analysis;Availability and the ability to come to the climbing intervention and to participate in the data collection;Living in the area limited by Zahle (N), Deir Zenoun, Marj (S), and Qab Elias/Bouarej (W).

Exclusion Criteria:Physical contraindications (pregnancy or other medical conditions that preclude climbing);BMI < 18.5 or >35.

### 2.4. Screening and Enrollment

To provide access to the climbing program to as many adolescents as possible and to ensure high representativeness of the sample, the adolescents are being recruited through several outreach channels (e.g., schools, other non-profits, social networks of current participants, social media, outreach campaigns in informal tented settlements). Informational material is being distributed and events are being held in schools and refugee camps to inform adolescents about the climbing program. A social media campaign is also being launched. Parents or (legal) guardians can use an online form to apply to participate in the program and, thereby, provide informed consent. If the inclusion criteria are met, the adolescents are then invited to attend a first trial session to determine whether they want to participate. If they are interested in participating, inclusion and exclusion criteria are verified by the study personnel, and the adolescents and their parents are asked to provide written informed consent. The written informed consent of the parents/legal guardians are gathered through personal communication between a trained staff member of ClimbAID and the respective guardian to make sure that every participant and their legal guardians understand the study conditions.

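### The exclusion criteria for climbing are verified only after the first trial session, for which the only stated condition is the inclusion criteria

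*Protocol article*

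**What the plan says.** Section 2.4 (Screening and Enrollment) describes a sequence.

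- Application: "Parents or (legal) guardians can use an online form to apply to participate in the program and, thereby, provide informed consent".
- Trial session: "If the inclusion criteria are met, the adolescents are then invited to attend a first trial session to determine whether they want to participate".
- Eligibility check: "If they are interested in participating, inclusion and exclusion criteria are verified by the study personnel". The adolescents and their parents are asked for written consent at this stage.

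Section 2.3 (Eligibility Criteria) lists four inclusion items: age, informed consent from the adolescent and the guardian, availability and ability to attend, and residence in a defined area. The exclusion items are a separate list: "Physical contraindications (pregnancy or other medical conditions that preclude climbing" and "BMI < 18.5 or >35".

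**The concern.** The first of the two exclusion items is, by its own wording, about who should not climb. A criterion of that kind protects people only if it is applied before they could climb. In Section 2.4 the step before the trial session refers to inclusion criteria, and the step after it refers to both inclusion and exclusion criteria. The exclusion check therefore sits behind the first contact with the programme.

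What is at stake is participant safety at that first session, and clarity about who records an event if one happens there. Nothing in the estimation or testing of the primary outcome depends on it.

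**Working it through.** No arithmetic applies, and the plan gives no figure on this point to reproduce. The check is a reading of Section 2.4 against Section 2.3, with a search of the rest of the article for an earlier health check.

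1. **Is the order fixed by the text?** Yes. Meeting the inclusion criteria leads to the trial session, and interest after that session leads to verification. Each step is conditional on the one before it.
2. **What must be met before the trial session?** Only the inclusion criteria are named. Going through the four items in Section 2.3, none concerns health. The item on ability concerns coming to the intervention and taking part in data collection.
3. **Where do the health items sit?** Only in the exclusion list of Section 2.3. Section 2.4 first mentions exclusion criteria at the step after the trial session.
4. **Is there an earlier check elsewhere?** None is described. Section 2.9.2 has medical conditions recorded in the questionnaire, but as a possible influencing or confounding variable, not as a condition for attending.
5. **Does the trial session involve climbing?** The article does not say. Its stated purpose is to let adolescents decide whether to join, and Section 2.5 describes each programme session as including climbing activities and games. Climbing at the trial session is therefore a reasonable inference and no more.
6. **What consent precedes the session?** The guardian's, through the online form. Section 2.3 also counts the adolescent's consent as an inclusion criterion, yet Section 2.4 first asks the adolescent for it after the session. Read literally, the inclusion criteria cannot all be met at the point where Section 2.4 requires them, so the two sections need reconciling in any case.
7. **Who records an event at the trial session?** The Discussion says that any accidents and potential adverse events will be documented, by the trainers or facilitators for the intervention group and by the study headquarters for the control group. At the trial session eligibility has not been verified, and no section places attendees in either group at that stage. Responsibility for recording is therefore unassigned.

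**The case against.** The strongest reply is that the phrase about meeting the inclusion criteria may be shorthand for a general first eligibility screen, and that verifying normally means confirming information already given. The online form could contain health questions, and an article need not print the form. This stands in part: the text does not exclude an earlier question, so it cannot be said that nobody asks about health before the session. But the article does not merely leave a detail out. It states an order, names inclusion criteria at one step and both sets at the next, and puts the study personnel's check after the session. An answer on a form would still be unverified when the adolescent attends.

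A second reply is that the session might be a visit or demonstration, in which case nobody excluded would climb. This also stands as a limit.

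Three stronger readings are tempting, and the document does not support them.

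- A reader might infer that adolescents attend without any consent. Section 2.4 says that the guardian consents by applying online. Only the written consent and the adolescent's own consent come later.
- A reader might infer that an injury at the session falls outside the adverse event definitions. In Section 2.12 only mild events are defined for the intervention group; the moderate and severe definitions name no arm or period. What is missing is narrower, namely who does the recording.
- A reader might apply an assumed contraindication rate to the target of 160. That target counts adolescents included in the study, who have by then passed verification. Those at issue are trial-session attendees later found ineligible, and the article gives neither their number nor a rate.

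**Conclusion.** The point holds as a fault in a stated sequence: the safety exclusions of Section 2.3 are verified after the first trial session, and no earlier check is described. Its practical weight rests on two assumptions: that the trial session includes climbing, and that the online form does not already screen for health. If either is false, the risk is smaller or absent, and a clarifying sentence would settle the matter. Its size in participants cannot be derived from the document. Because the target sample size in Table 1 is accompanied by a recruitment status of complete, a change cannot protect those already recruited; its value lies in later cycles and in any reuse of the protocol.

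**What to change.** Reconcile Sections 2.3 and 2.4 with three short changes.

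- Place the study personnel's existing exclusion check before the trial session. If health is already screened at application, say so instead. The criteria themselves are not in question here.
- State that any event at the trial session is recorded, and by whom.
- Say when the adolescent's own agreement is obtained relative to the session. The written consent step need not move, since the guardian has already consented through the online form. Leaving it in place avoids a personal contact with the guardian of every adolescent who later declines.

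The cost is a few sentences of text and an exclusion check on some adolescents who then decide not to take part.

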### 2.5. Intervention

Since 2017, the “Climbing for Peace” project of the Swiss nonprofit organization ClimbAID has been using climbing as a tool to build inclusive communities, improve mental well-being, and address social problems in projects with young people from host and refugee communities in Lebanon. The PSS program “YouCLIMB” investigated in this study is based on climbing therapy and experiential education. It was developed to improve the physical and mental well-being of young people and to help them develop social and life skills. The activities are being led by four local facilitators who are trained by a certified climbing instructor (Swiss J + S Course Instructor Sport Climbing). In addition to the sport-specific training, the coaches are trained in PSS facilitation, child protection, and mental health first aid and are supervised by a social worker and a climbing therapist.

Each session begins with a welcome, a reminder of the group rules, and an introduction to the theme and goals of the session. After a breathing meditation exercise, there is a warm-up routine, which is jointly led by the group. In the activity part of the session, the group works through experiential climbing activities and games that are designed to convey and experience the objectives of the session. 

Session 3, for example, features the game “Three-legged Climbing” to demonstrate the module topic of teamwork and cooperation. In this game, two players are connected by a string at their ankles and must work together to climb on a climbing wall. Success requires full focus, empathy, clear communication, trust, and respect—all elements of teamwork and cooperation.

Sessions 5 and 6 focus on communication and conflict resolution, providing theoretical insights such as the “four sides of communication” by Friedemann Schulz von Thun [46] and “compassionate communication” by Marshall Rosenberg [47]. These concepts are applied through activities and games on and off the climbing wall, followed by group discussions to reflect on experiences and apply them to real-life situations. After a mindfulness or meditation exercise, the session ends. The associated session-specific topics can be found in Table 2.

The CG initially receives no climbing intervention, but all participants are rewarded with 100,000 LBP (between $2.80 and $3.60 USD depending on the daily rate) after completing the posttest. After completing the IG-CG climbing cycle (8 weeks), participants in the CG will also be given an opportunity to participate in the YouCLIMB program.

### 2.6. Allocation to the IG and CG

Due to culture-specific requirements and for organizational reasons, stringent randomization is not possible. For example, due to school exams, many participants are limited to only one of the three cycles. Some female participants are only allowed to participate if they are accompanied by another member of the family. To navigate this and to increase adherence to the intervention, the timing of the intervention (immediately = IG, 3 months later = CG) can be self-selected by participants, providing they are available at each time point when data are being collected. In addition, we are accommodating special requirements (e.g., women-only groups, groups for those who can only participate if accompanied by a specific person). Out of the actual eligible applicants, about 20% stated that their availability was limited to one of the three cycles. We are allowing such applicants to self-select the timing of their participation, thereby determining their classification as either CG or IG participants.

Remaining participants are being allocated randomly. First, each applicant is being assigned a random number by using Microsoft Excel’s “=RAND()” function. Then, applicants are being allocated to the CG or IG based on the parity of the random number’s thousandth digit, whereby if the thousandth digit is even, the applicant is allocated to the CG, otherwise the participant is allocated to the IG. 

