### 2.7. Sample Size Estimation

Power calculation was performed using G*Power software [48] (University of Duesseldorf, Germany) with a two-tailed alpha of 0.05, a beta of 90%, and an estimated effect size of Cohen’s d = 0.55. This resulted in a necessary sample (as treated AT) of at least 52 members per group at posttest. 

As the dropout rate is difficult to foresee in the current political and economic situation, we assumed a drop-out rate of 35% per intervention cycle. Thus, we need to enroll 80 participants in the IG and the CG, respectively. Hence, at least 160 adolescents need to be included in the study, distributed across the six climbing groups (each consisting of 12–14 participants) and the control group. Including the waitlist-control group (which will be offered the intervention after the study period), up to a total of 160 adolescents should thus be provided with a climbing program. Figure 2 gives an estimated overview about sample sizes.

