The strengths of the study are the large sample size, the existence of a control group, the mixed-methods approach, the use of manualized treatment options, the naturalistic setting, and therefore, the pragmatic nature of the evaluation of a real-world program. One limitation is the lack of randomization. In this specific study, randomization may also have been a limitation because it may have resulted in the exclusion of female participants for cultural reasons. Being female in a refugee context is a risk factor for mental distress, especially depression [38]. Syrian refugees in Lebanon often live according to religious or cultural traditions with a strong desire to protect girls from potential harmful encounters outside the family. To include female participants, we decided not to randomize the group to allow family members who also need to comply with the inclusion criteria (e.g., mostly brothers, sisters, cousins) to participate together in the same intervention group. In addition, we offered female-only groups, and ClimbAID staff travel on the buses that collect all the participants from their homes. No participants must use public transportation. We therefore concluded that the disadvantages of randomization (which would prevent a vulnerable group from participating in the intervention) outweighed the positives. If the groups differ at baseline in relevant factors, appropriate statistical methods (e.g., propensity score matching) will be applied.

Another potential limitation is that the bouldering intervention cannot be blinded with respect to facilitators or participants. All outcome measures are self-assessed and, therefore, are also not blinded. Third, in the absence of exclusion criteria regarding possible diagnoses or levels of psychological distress, it is possible that we will obtain a heterogeneous sample, with the associated advantages of a naturalistic design and low-threshold intervention and the disadvantages of potentially diluted intervention effects.

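### Allocation mixes self-selected and randomised participants, and the planned pooled analysis ignores the known route, so the randomised comparison is never reported on its own

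*Protocol article*

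**What the plan says.** Section 2.6 says that strict randomisation is not feasible and gives reasons. One is that "due to school exams, many participants are limited to only one of the three cycles"; another is that some girls and young women may attend only with a relative. About 20% of eligible applicants reported that they could attend only one cycle. Of these the plan says: "We are allowing such applicants to self-select the timing of their participation, thereby determining their classification as either CG or IG participants". It continues: "Remaining participants are being allocated randomly", by the parity of a digit of a spreadsheet random number. The same section also accommodates women-only groups and people who must be accompanied. One sentence appears to offer a choice of timing to participants in general, provided they can attend each data collection.

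The Discussion (section 3) reads differently: "One limitation is the lack of randomization". It adds that the decision was not to randomise, so that family members could join the same group.

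Section 2.11.1 plans mixed ANOVAs of time × group, per protocol first and by intention to treat as a sensitivity analysis. It also plans a baseline comparison of the arms, regression to look for confounders, and a method such as propensity score matching if important sociodemographic variables differ significantly. Allocation route does not appear. Section 2.9.2 lists the recorded possible confounders: sociodemographic data (including age and school enrolment), physical activity, medical conditions and climbing experience.

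**The concern.** For a randomised participant, arm is independent of everything else about that person. For a self-selector, arm follows from whatever made only one cycle possible. If that reason also affects how well-being moves over the eight weeks, the self-selected part of the contrast is confounded, and the single pooled estimate carries a share of that confounding.

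Route is known by design, so it needs no baseline test to reveal it. A matching step triggered by significance tests in about 80 per arm can stay inactive while a relevant imbalance remains, and it considers measured sociodemographic variables only.

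The primary causal claim is at stake. Readers of the Discussion would take the whole trial as non-randomised, although section 2.6 implies that a majority may have been randomised. Readers of section 2.6 might credit the pooled result with more protection than it has. Neither would see the one estimate that randomisation protects.

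**Working it through.** **Inputs from the document.** Two-sided alpha 0.05; d = 0.55; 52 per group at posttest; 35% dropout; 80 per group enrolled, 160 in total (section 2.7). About 20% limited to one cycle (section 2.6).

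**Input not in the document.** The difference in pre-post change between self-selected IG and CG members, for reasons other than the intervention. Assumed range: 0.2 to 0.8 SD.

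**1. The plan's own figure.** n per group = 2(z₁₋α/₂ + z_power)² / d².
- 80% power: 2(1.960 + 0.842)² / 0.3025 = 51.9, so 52 (53 with the t distribution).
- 90% power: 2(1.960 + 1.282)² / 0.3025 = 69.5, so 70 (71 with t).
- Dropout: 52 / 0.65 = 80 per group, 160 in total, as stated.

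The stated 52 therefore matches 80% power, although section 2.7 gives "a beta of 90%, and an estimated effect size of Cohen’s d = 0.55". That mismatch is a separate matter. Here 52 per arm is taken as planned, with power 80% (normal) or 79% (t).

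**2. Size of the two routes.** 0.20 × 160 = 32 self-selected, leaving at most 128 randomised, 64 per arm. After dropout: 64 × 0.65 = 41.6, about 42 per arm.

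**3. Shift of the pooled estimate, self-selectors split evenly.** Shift = 0.20 × assumed difference. SE = √(2/52) = 0.196. Type I error = P(|Z + shift/SE| > 1.96).

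| Assumed difference in change (SD) | Shift (SD) | Shift as share of 0.55 | Type I error |
|---|---|---|---|
| 0.2 | 0.04 | 7% | 5.5% |
| 0.3 | 0.06 | 11% | 6.1% |
| 0.5 | 0.10 | 18% | 8.0% |
| 0.8 | 0.16 | 29% | 12.9% |

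The difference must be in change. A stable difference in level cancels in the time × group term.

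**4. Uneven split.** If all 32 self-selectors entered one arm, they would form 32/96 = one third of it and none of the other. If their change differed from that of randomised participants by 0.2 to 0.5 SD, the shift would be 0.07 to 0.17 SD.

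**5. Power of a randomised-only comparison at d = 0.55 (t distribution).**

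| Placed non-randomly | Completers per arm | Power |
|---|---|---|
| 20% | 41.6 | 70% |
| 30% | 36.4 | 64% |
| 40% | 31.2 | 57% |

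At 42 per arm the 95% interval half-width is 1.96 × √(2/42) = 0.43 SD, against 1.96 × √(2/52) = 0.38 SD pooled.

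**6. Would a test of arm × route help?** With about 10 self-selected and 42 randomised completers per arm, SE = √(2/10 + 2/42) = 0.50. Power for a 0.5 SD difference is about 17%. A non-significant result would reassure no one.

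**The case against.** The article is open about the weakness. It says strict randomisation was not possible, explains why, names this as a limitation, and plans a baseline comparison, a confounder regression and conditional matching. Covariates such as route and cycle are often left to an analysis plan, which is not shown. All of this stands, and a reader should not infer that nothing was planned. But the article does fix the primary comparison and the trigger for adjustment, and neither uses route. The conflict between sections 2.6 and 3 is in the article itself.

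Several stronger readings are tempting and are not supported:

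- **The randomised evidence is discarded.** It is not. On the 20% figure about four fifths of the pooled data are randomised and drive the estimate. What is missing is a separate report of them.
- **Exam pressure biases the result in a known direction.** No section says when exams fall relative to the two surveys. Exams could push a participant towards either arm, and school enrolment and age are recorded.
- **The type I error is 8% or more.** That needs a difference of about 0.5 SD in change among self-selectors, for which the article gives no figure. At 0.2 to 0.3 SD it is 5.5% to 6.1%.
- **128 participants are certainly randomised.** This is an upper bound. The 20% refers to eligible applicants, and those placed with relatives or in special groups may add to the non-random share.

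**Conclusion.** The point holds as a flaw in how the comparison is set up, not as a demonstrated bias. The plan combines a randomised and a self-selected comparison, knows which participant belongs to which, and uses that knowledge nowhere in the stated analysis. Its safeguards do not make up for this.

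The numerical consequence, a shift of 0.04 to 0.16 SD and a type I error of about 5.5% to 13%, rests on four assumptions: 20% self-selected, an even split, 52 completers per arm, and a 0.2 to 0.8 SD difference in change. Confidence is high for the allocation facts and the contradiction between sections 2.6 and 3. It is low for the size of any bias, and there is no basis for stating its direction.

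**What to change.** 1. From the allocation records, give every participant a route flag: randomised, self-selected, or placed with a relative or in a special group. Record also the cycle in which the participant was studied.
2. Stratify the full-sample model by route and cycle. This removes bias from an uneven mix of routes between arms, but not confounding within the self-selected stratum, so step 3 is also needed.
3. Name as a key analysis the effect among randomised participants only, analysed by allocated arm. A per-protocol version could undo the randomisation, given the 35% dropout assumed. Report it beside the pooled estimate.
4. Rest the causal claim on the randomised estimate and label the pooled one as partly non-randomised. Do not rely on an arm × route test, which has too little power. Do not rely on agreement of the two estimates either, because they share most of their data.
5. Reconcile sections 2.6 and 3 on who was randomised, and report the numbers by route.

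The cost is one flag and one further analysis. Table 1 lists recruitment as complete, so the flag depends on the allocation records. The article reports a 20% figure, which suggests that availability was recorded. The price in precision is at most about 70% power at d = 0.55 in the randomised stratum against about 79% pooled, and less if more than 20% were placed non-randomly.
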